**Methods/Design:**

Ninety participants will be recruited from the physiotherapy departments of three teaching hospitals and randomly allocated to treatment or control groups using a concealed procedure. All participants will perform an exercise programme. Participants in the treatment group will also receive joint mobilisation twice a week for four weeks. Blinded follow-up assessments will be conducted four, 12 and 24 weeks after randomisation. The primary outcome measures will be the Lower Extremity Functional Scale and the Assessment of Quality of Life. Secondary outcomes will include measures of impairments, activity limitation and participation. Data on the use of physiotherapy services and participants' out-of-pocket costs will be collected for the cost-effective and cost-utility analyses. To test the effects of treatment, between-group differences will be examined with analysis of covariance using a regression approach. The primary conclusions will be based on the four-week follow-up data.

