### Participants

Participants will be recruited following cast removal from the plaster clinics and physiotherapy departments of three large teaching hospitals in Sydney, Australia (Royal North Shore Hospital, Royal Prince Alfred Hospital, and St Vincent's Public Hospital). The inclusion criteria will be:

• ankle fracture treated with cast immobilisation with or without surgical fixation

• cast removed in the preceding seven days

• approval from the orthopaedic specialist to weight-bear as tolerated or partial weight-bear

• referral to outpatient physiotherapy for treatment

• at least 2 out of 10 pain in the ankle when up to 50% of body weight is borne through the affected leg

• completed skeletal growth assessed by the union of epiphyses on radiographs

• no concurrent and significant injuries or pathologies which may affect the recovery of the participant's lower limb function, and

• available for the six month follow-up period.

In addition to recruiting from multiple sites, other strategies will be used to maximise recruitment rates [40]. A log will be designed to aid the screening of potential participants at each site, and will be monitored by the investigators. Posters about the trial, inservices and regular communication with the participating physiotherapy departments will also assist to facilitate recruitment rates.

Ethical approval will be obtained from the ethics committee of each participating site (i.e., the University of Sydney Human Research Ethics Committee, Northern Sydney Health Human Research Ethics Committee, Sydney South West Area Health Service Ethics Review Committee (RPAH zone), and the St Vincent's Hospital Human Research Ethics Committee).

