Twelve secondary outcome measures will be used (Table 1). All participants will be given a calendar on which to mark the first day they can walk pain-free for 10 metres at a comfortable cadence. This will be used to calculate the number of days to pain-free walking from cast removal.

Walking speed and step length asymmetry will be measured as the participants walk unaided along a 14-metre walkway. The average of three attempts will be used for data analysis. Participants will be instructed to walk as fast and as well as possible. Their time to walk the central 10 metres will be recorded by a stop watch, and walking speed will be calculated by dividing the distance covered by the time elapsed. A six-metre long, one-metre wide mat marked with five-centimetre grids will be taped to the floor over the central six metres of the walkway. Participants will be videotaped as they walk across the mat. Step length asymmetry (i.e., the difference in step length between the affected and unaffected sides) will be calculated by playing the video recording in slow motion, and digitising the heel position of each footfall on a customised computer programme [47]. This method has high inter-rater, intra-rater and concurrent reliability [47-50].

Stepping rate on stairs will be calculated by the participants climbing four steps three times as fast as possible without using handrails. This task is part of the Motor Assessment Scale [51]. Although its psychometric properties have not been examined in people with musculoskeletal complaints, stair climbing will be included as an outcome measure as it is reasonably challenging and is a commonly-performed activity.

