### Statistical analysis

Data analysis will be undertaken at the completion of data acquisition and will be by intention to treat (that is, participants will be analysed according to group allocation regardless of compliance) [60]. Missing data will be replaced by the last known value carried forward. The statistician will be given coded data to ensure blinding.

Separate analyses will be performed on the four, 12 and 24 week data, with the four-week (i.e., the end of the intervention period) follow-up being the primary time point for analysis. To test the effects of treatment, between-group differences will be examined with analysis of covariance using a regression approach. The emphasis will be on estimation, but hypothesis tests will also be conducted (alpha = 0.05). Pre-test scores will be entered into the model as the only covariate.

In a secondary analysis designed to test the influence of fracture severity on treatment effects, additional terms (fracture severity, group by fracture severity interaction) will be entered into the regression model. Fracture severity will be categorised into two levels based on the number of malleoli involved: less severe (unimalleolar fractures) and more severe (bimalleolar or trimalleolar fractures). The effect of fracture severity on treatment will be determined by examining the interactions between group of allocation and fracture severity.

Ninety participants (45 per group) will participate in the trial. This sample size provides a 90% probability of detecting a difference between group means of 10 points on the Lower Extremity Functional Scale, assuming a standard deviation of 12 based on a recently published study [41]. These calculations assume a correlation of 0.6 between pre- and post-test measures and an alpha of 0.05, and allowed for 10% dropouts and 20% non-compliance.

The economic evaluation will consist of cost-effectiveness and cost-utility analyses. The cost-effectiveness analysis will use the Lower Extremity Functional Scale as a measure of effectiveness. The cost-utility analysis will use the Assessment of Quality of Life as a measure of utility [43]. The analyses will examine differences between treatment and control participants in terms of costs incurred and reductions in perceived disability (cost-effectiveness analysis) or utility gained (cost-utility analysis).

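### Days to pain-free walking is a right-censored time to event, and the one stated analysis rule (ANCOVA on a pre-test score, last value carried forward) does not fit it

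*Protocol article*

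**What the plan says.** Protocol article, Outcome assessment: "All participants will be given a calendar on which to mark the first day they can walk pain-free for 10 metres at a comfortable cadence". The next sentence defines the variable: "This will be used to calculate the number of days to pain-free walking from cast removal". It is one of twelve secondary outcomes.

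Protocol article, Abstract (Methods/Design): "Blinded follow-up assessments will be conducted four, 12 and 24 weeks after randomisation". Follow-up therefore ends at day 168 after randomisation.

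Protocol article, Participants: entry requires "cast removed in the preceding seven days", so the clock for this outcome can start up to seven days before enrolment.

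Protocol article, Statistical analysis: "To test the effects of treatment, between-group differences will be examined with analysis of covariance using a regression approach". On covariates: "Pre-test scores will be entered into the model as the only covariate". On missing data: "Missing data will be replaced by the last known value carried forward". The analyses are run separately on the 4-, 12- and 24-week data, with week 4 primary, and by intention to treat. No outcome is exempted, and neither censoring nor a time-to-event method is mentioned.

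**The concern.** The number of days exists only for a participant who reaches the event while under observation. For the rest we know only that the time exceeds their last contact. The stated rule has no means of using that information.

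If the regression runs on whoever has a value, it conditions on recovery, which happens after randomisation and may depend on treatment. If mobilisation speeds recovery, more controls than treated participants are still unrecovered at the end. The slowest controls then drop out of the comparison and the benefit looks smaller than it is. If mobilisation slows recovery, the harm is understated in the same way.

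The Background section gives earlier return to activities as the reason for using mobilisation. This outcome measures speed of recovery directly, so a diluted estimate of it would matter to readers even though it is secondary.

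**Working it through.** **1. Does the stated rule fit the outcome?**

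- Covariate: "Pre-test scores will be entered into the model as the only covariate". Days to the first pain-free walk has no baseline score.
- Missing data: "Missing data will be replaced by the last known value carried forward". The outcome is recorded once or never, so there is no earlier value to carry.
- Time points: separate 4-, 12- and 24-week analyses. The outcome is one quantity per person, not a repeated measurement.

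The rule fails on all three counts. Two defaults remain:

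- *Use only those with a value.* This is what regression software does. Steps 2 to 4 give its size.
- *Assign a value at the end of follow-up.* This treats unrecovered people as recovered on that day. Take exponential times, a control median of 60 days and hazard ratio 1.5. The difference in mean recovery time is (60/ln 2) × (1 − 1/1.5) = 28.9 days, but capping at day 168 gives 19.6. That figure is a valid restricted mean difference only if it is labelled as one and nobody is lost early. Assigning the date of last contact to people lost early would be biased even for the restricted mean.

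**2. Inputs for the size**

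From the article: 45 per group, follow-up to day 168, alpha 0.05 (taken as two-sided). The article states no figure for this outcome, so there is none to reproduce; its sample size calculation concerns the Lower Extremity Functional Scale.

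Assumed, because the article gives no values: exponential recovery times, recovery hazard ratio 1.5, 50% to 95% of controls pain-free by day 168, no early loss, and time counted from randomisation.

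**3. Formulas and one worked case**

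With hazard λ and C = 168:

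- restricted mean = (1 − e^(−λC))/λ
- mean among the recovered = 1/λ − C·e^(−λC)/(1 − e^(−λC))

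With 80% of controls recovered, λ = −ln(0.2)/168 = 0.00958 for controls and 1.5 × 0.00958 = 0.01437 for treated. The unrecovered fractions are 0.20 and 0.2^1.5 = 0.089.

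- Restricted means: 0.80/0.00958 = 83.5 and 0.911/0.01437 = 63.4 days; difference 20.1.
- Means among the recovered: 104.4 − 42.0 = 62.4 and 69.6 − 16.5 = 53.1 days; difference 9.3.

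**4. Simulation over the range** (1,500 trials per row, hazard ratio 1.5; differences are days in favour of treatment)

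| Controls recovered by day 168 | Unrecovered of 90 | Difference, recovered only | Restricted mean difference, all | Power, recovered only (t-test) | Power, all (Cox) |
|---|---|---|---|---|---|
| 95% | 3 | 11.7 | 16.1 | 31% | 44% |
| 90% | 6 | 10.8 | 18.4 | 23% | 45% |
| 80% | 13 | 8.8 | 19.6 | 14% | 41% |
| 70% | 21 | 7.3 | 19.9 | 11% | 39% |
| 50% | 38 | 4.6 | 16.7 | 6% | 29% |

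The 80% row agrees with the closed form within simulation error. The Schoenfeld formula gives power of 32%, 41% and 45% for 54, 72 and 81 events, in line with the last column. At hazard ratio 1.0 both tests reject in about 4% to 6% of trials.

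The two power columns differ in the test as well as in the participants used, so not all of the gap is due to the lost participants. The two difference columns do not have this problem.

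**5. A second setting**

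With a control median of 60 days, the unrecovered fractions at day 168 are 2^(−168/60) = 14.4% for controls and 2^(−1.5 × 168/60) = 5.4% for treated. The restricted mean difference is 19.6 days, against about 10 days among the recovered.

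**The case against.** **The article does not say that unrecovered participants are dropped.** A reader might infer that it does. That is not supported: the Statistical analysis section commits to intention to treat and gives no rule, either way, for people who never become pain-free. Using recovered participants only is the default result of the stated method when nothing can be carried forward. The figures above describe that default, not a stated exclusion. This objection stands.

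**The analysis paragraph is general.** Satisfaction is measured only at week 4 and global perceived effect is itself a rating of change, so neither has a natural pre-test score. A condensed article may leave a special method for one secondary outcome to a fuller document. This stands in part: such a document may already contain the method. But the article does more than stay silent. It fixes one model, one covariate and one imputation rule for treatment effects without exception, and a plan that followed it would inherit the misfit.

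**The time origin is harmless.** A reader might infer that counting from cast removal biases the comparison, because up to seven days precede enrolment. It does not. The delay comes before concealed randomisation in both arms and is balanced in expectation. Entry also requires ankle pain on partial loading, so pain-free walking during those days is unlikely. Counting from cast removal is a legitimate definition.

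**The consequence is limited.** The recovery rate, hazard ratio and distribution are all assumed, type I error holds, and even the censored analysis has under 50% power at hazard ratio 1.5. All of this is correct, and it keeps the point at the level of a secondary outcome.

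**Conclusion.** The point holds in this form: the outcome is right-censored, the only stated rule cannot be applied to it, and the handling of participants not pain-free by 24 weeks is left open. If the regression falls back on recovered participants, the estimated difference shrinks from about 16–20 days to about 5–12 days, and power falls from about 29–45% to about 6–31%. These ranges rest on exponential times, a hazard ratio of 1.5 and 50% to 95% of controls recovered by day 168. The loss is smallest when nearly everyone recovers and grows as more do not; the article does not say which case to expect. The distortion runs toward no difference and creates no excess of false positives. The two primary outcomes and the week-4 conclusions are untouched. The change is worth making because it is cheap, but it is not a threat to the trial's main result.

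**What to change.** In the Statistical analysis section, exempt days to pain-free walking from the ANCOVA and carry-forward sentences and add wording along these lines: time to the first pain-free 10-metre walk will be described by Kaplan-Meier curves and compared by a log-rank test or Cox model stratified by site. Participants not pain-free will be censored at last contact or week 24, whichever is earlier. The difference in restricted mean time to day 168 will be reported with its confidence interval.

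The restricted mean difference keeps the result in days and suits the article's preference for estimation over testing.

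Optional refinement, not a correction of bias: count time from randomisation, with days since cast removal as a covariate. If cast removal stays as the origin, treat the interval before enrolment as delayed entry.

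Cost: analysis wording only. The calendar supplies the event dates and the follow-up visits supply the censoring dates. No extra data, participants or visits are needed.

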In this pragmatic trial, participants will be seen at a frequency typical to that which occurs in the clinical setting. Participants in the treatment group will receive two treatment sessions per week for four weeks for joint mobilisation and progression of the exercise programme. Participants allocated to the control group will receive two treatment sessions in the first week, then one session per week for three weeks. In the first session, participants in the control group will be taught the exercises, which will be monitored and progressed in subsequent sessions.

In addition, at the treatment sessions all participants will receive gait retraining, progression of walking aids, and advice on prognosis and return to activities. If required, participants will receive ice for pain relief, and compression and elevation for the management of swelling. No other physiotherapy treatments will be administered during the four-week intervention period.

After each initial treatment session, the treating physiotherapist will receive a phone call from an investigator unblinded to group allocation. Implementation of the experimental protocol for each participant will be discussed to ensure compliance.

At the end of the intervention period, passive joint mobilisation treatment will cease and participants will be allowed to be progressed to exercises other than those in the standardised set. Ankle taping can be performed to assist return to sports.

The timing of discharge will not be dictated in the protocol. Participants will be discharged by their physiotherapists when they return to their previous level of function, reach a plateau in their progress, or choose to discontinue treatment.

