Satisfaction with physiotherapy treatment will be measured at the four-week follow-up assessment on a 100-mm visual analogue scale marked "completely unsatisfactory" at one end and "best possible" at the other. At all follow-up assessments, participants will be asked if the physiotherapy treatment has had any negative effects and, if so, the nature of the effects. They will also record whether they have had treatment other than physiotherapy for the fractured ankle.

The treating physiotherapist will complete a survey for every participant at each follow-up assessment until discharge. Information gathered on this survey will be: the date and reason of discharge (if applicable), number of physiotherapy sessions scheduled, number of physiotherapy sessions attended, exercises prescribed and repetitions completed, any other physiotherapy treatment administered, and, for the treatment group only, the dates, number of sets and duration of the joint mobilisation treatment. This information will be analysed to obtain the length of physiotherapy required, percentage of scheduled sessions attended, compliance of participants to the exercise programme, and compliance of physiotherapists to the experimental protocol.

Data will be collected on paper forms and manually entered into a computer programme. Several strategies will be implemented to ensure the accuracy of the data. Data collection forms will be checked for completion. Data entry will be performed twice and the two entries will be compared to check for errors. Range checks will be performed on outcome values at the completion of data entry.

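### The only described harm question depends on what unblinded participants blame on physiotherapy, is first asked after all eight scheduled mobilisation sessions, and has no matching harm item on the therapist survey

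*Protocol article*

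**What the plan says.** Under Outcome assessment, the protocol article describes one harm question: "At all follow-up assessments, participants will be asked if the physiotherapy treatment has had any negative effects". Those who say yes are asked what the effects were. The question is put at the follow-up assessments, which the abstract places as follows: "Blinded follow-up assessments will be conducted four, 12 and 24 weeks after randomisation". Statistical analysis fixes where the first of these falls: "with the four-week (i.e., the end of the intervention period) follow-up being the primary time point for analysis".

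Interventions sets the treatment schedule. For the treatment group: "Participants in the treatment group will receive two treatment sessions per week for four weeks for joint mobilisation and progression of the exercise programme". The control group has "two treatment sessions in the first week, then one session per week for three weeks". The one investigator contact described during treatment is about implementing the protocol: "After each initial treatment session, the treating physiotherapist will receive a phone call from an investigator unblinded to group allocation".

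Outcome assessment also lists what the treating physiotherapist's survey collects: when and why the participant was discharged, sessions scheduled and attended, exercises, other physiotherapy given and, in the treatment group, details of the mobilisation. No harm item is among the listed fields. The Discussion states that neither participants nor physiotherapists can be blinded. Statistical analysis fills missing data with the last known value and states no exception.

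**The concern.** The question asks participants for a causal judgement. Someone whose ankle becomes more painful or swollen, or who goes back to a doctor, answers yes only if they hold physiotherapy responsible. In both arms the recent fracture is an obvious alternative explanation. In the treatment arm there is also a hands-on procedure to credit or blame. The tendency to attribute a problem to physiotherapy may therefore differ by arm, in either direction, without any difference in what happened to the ankles.

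Timing adds to this. The first question looks back over the whole treatment course, and no harm field on the therapist's survey covers a participant who cannot be asked. The Discussion intends the results to inform rehabilitation guidelines. A report of few or no negative effects, gathered this way, would be weak evidence that adding mobilisation is well tolerated.

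**Working it through.** The plan states no figure for harm, so there is none to reproduce. The check is a count of sessions, a comparison of dates and a short argument about what the question measures.

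**1. Sessions before the first harm question (Interventions).**
- Treatment: 2 per week × 4 weeks = 8.
- Control: 2 + (1 × 3) = 5.

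**2. Timing (abstract; Statistical analysis).** The first follow-up is at week 4, the end of the intervention period. All 8 scheduled mobilisation sessions come before it. If each asking covers the time since the previous assessment, the recall windows are:
- baseline to week 4: 4 weeks
- week 4 to week 12: 12 − 4 = 8 weeks
- week 12 to week 24: 24 − 12 = 12 weeks.

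**3. What the question measures.** Let p be the proportion in an arm with a real worsening, and a the proportion of those who blame physiotherapy for it. The proportion answering yes because of a real worsening is p × a. If the true rate is the same in both arms, the ratio of reported harm is

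(p × a_T) / (p × a_C) = a_T / a_C.

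This equals 1 only if the arms attribute alike. The article gives no information on a_T or a_C, so the direction and size of the distortion cannot be stated. With unblinded participants, nothing in the design makes the two equal.

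**4. Participants who cannot be asked at week 4.** Statistical analysis allows for 10% dropout: 0.10 × 45 = 4.5, or about 4 to 5 per arm. The article does not say when they are lost. On the plan's own allowance, between none and about 4 to 5 per arm could be gone before any harm question is asked. The separate 20% non-compliance allowance, 0.20 × 45 = 9 per arm, does not belong here. Analysis is by allocation regardless of compliance, and those participants are still due their assessments.

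**5. Carrying values forward.** No baseline harm value is described, so the rule cannot create a no at week 4. Read literally, it would carry a week-4 no to weeks 12 and 24 for a participant lost later.

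**The case against.** The strongest objection is that much of this is silence in a condensed article. Procedures for reporting adverse events during treatment commonly sit in the full protocol, which is not shown. That stands. A reader might infer that no harm reaches an investigator while mobilisation is being given, but the article does not support this. It shows only that the one contact it describes concerns compliance.

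A reader might also infer that participants whose treatment is stopped by harm are counted as having none. The documents do not support that either. Stopping treatment is not the same as leaving follow-up, so such participants can still be asked at weeks 4, 12 and 24. No rule turns a missing week-4 answer into a no. Nor are the discharge reasons a closed code list. The article says participants are discharged "when they return to their previous level of function, reach a plateau in their progress, or choose to discontinue treatment", which describes practice in prose. The survey's discharge-reason field has no stated categories, and the survey also records attendance, so early stopping would be visible.

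Other data give partial signals that do not require blaming physiotherapy. These are the −5 to +5 rating of symptom change, the pain scales, the record of non-physiotherapy treatment for the ankle and, from week 4 to week 24, the four-weekly economic survey, which covers use of health and hospital services. This narrows the gap but does not close it. None of these is designated as a harm measure, and the economic survey starts only once the intervention period has ended.

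What the objection leaves intact is what the article does fix: the wording of the question, its timing and the listed fields of the therapist's survey.

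**Conclusion.** The concern holds in a limited form. As described, harm is elicited retrospectively, at weeks 4, 12 and 24 only, and through the attribution of unblinded participants. The first asking follows all 8 scheduled mobilisation sessions, and the listed survey fields offer no harm item as a second source. A between-arm comparison of the answers could differ from the comparison of events by the factor a_T / a_C, which the documents do not let anyone estimate. Events may go unrecorded in participants lost before week 4, who are at most about 4 to 5 per arm on the planned dropout.

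This rests on two assumptions: that the question is put as the article words it, and that no separate harm record exists in the unseen full protocol. If one does exist, the point about missed events weakens. The point about attribution still applies to this question. The primary analysis is not affected. The change is worth making because it is cheap and bears on what the trial can claim about safety.

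**What to change.** 1. **Reword the participant question, identically for both arms.** Ask about any new or worsened problem with the affected leg and any unplanned medical contact since the last assessment (since baseline at week 4), whatever the believed cause. Record the onset date and whether treatment was changed or stopped. Ask for perceived cause as a follow-on item. Base the between-arm harm comparison on the cause-neutral answer.
2. **Extend the physiotherapist's existing survey.** Add a harm item, and a stopping or discharge reason for negative effects. Report these data separately from the participant question, because scheduled contact of 8 against 5 sessions gives the treatment arm more opportunity for harm to be noticed.
3. **Exempt harm from carrying values forward.** Leave a missing answer missing, and report by arm and visit how many participants were asked.

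The cost is wording on two existing forms, with no new visits. Forms become slightly longer and more minor complaints will be recorded. The article does not say who asks the question. If it is the blinded assessor, an answer about changed treatment could reveal allocation, so that item is better completed by the participant in writing.
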